### Interventions

#### Overall intervention structure

The intervention phase consists of 6 weeks of music therapy, composed of 12 sessions, with two sessions per week (see Fig. 1). The length of each session is 60 min. The trial will not interfere with any concomitant treatments the clients may already be receiving or that may be required during the trial. The clients are informed of their right to leave the trial at any point without the need to give any justification. The content and working principles concerning IIMT and the additional components (LH and RFB) are described in the following sections.

#### Integrative improvisational music therapy

Integrative improvisational music therapy (IIMT) is used as the therapy model for all of the intervention conditions. IIMT is a model developed at our site [12] and successfully employed in our previous RCT for depression [2]. As described in the Introduction, the non-verbal expression and interaction of clinical improvisation typically leads to the emergence of abstract and unshaped mental contents, often accompanied by emotional loading. The evoked emotions, emotional memories, images, metaphors, and associations can then be further processed on the verbal domain, which creates the possibility for meaning formation [12].

Similar to the prior RCT, IIMT in the current RCT will consist of: 5–10 min of initial discussion; improvising in a client–therapist dyad with easily approachable instruments (drums and electric piano); and discussing the experiences triggered by the improvisations [12]. The number and length of the improvisations can vary depending on the client’s situation and the phase of the therapy process. Occasionally, clients may have difficulties verbalising their experiences, in which case the interaction may rely more on music. It may also be the other way around, whereby a client has a strong need to verbalise his/her musical experiences, thus creating less room for music. In other words, although based on a single music therapy technique (clinical improvisation), IIMT offers flexibility as well.

#### Added component: listening homework

LH will be conducted as an activity carried out outside the therapy context, in the client’s own time. This activity can be described as homework, which is a known practice particularly in cognitive and behavioural psychotherapies. In that field, two meta-analyses [45, 47] have been conducted, showing that homework compliance is significantly related to the therapeutic outcome, with the effect size varying from small to medium. What is important to our study is the fact that, according to the findings from cognitive and behavioural psychotherapies, the clients with depression particularly seem to benefit from homework.

In our study, the music listening homework specifically aims to foster the emotional processing associated with the clinical themes and experiences associated with the music improvisations created during the sessions. As described in the Introduction, music psychology research has widely evidenced the potential of music listening to serve as a forum for self-referential (and even auto-therapeutic) processing of emotional content.

In practice, the clinical improvisations are recorded during the music therapy sessions. A specially developed computer application allows each client to have personal access to his/her recorded improvisations on the university server. Clients will be able to listen to the music whenever they want and as many times as they want throughout the therapy process. This application also monitors the listening behaviour (frequency and duration), thus allowing us to evaluate the clients’ adherence to the task. While clients have access to all of their improvisations throughout the therapy process, however, after each session the clients are encouraged to listen to the clinical improvisations of that session, and the therapist may recommend particular improvisations. Experiences of listening back to improvisations are discussed and reflected upon with the therapist during the subsequent therapy session(s).

#### Added component: resonance frequency breathing

RFB is the second tool we wish to use for promoting self-reflective emotional processing. RFB, in its stand-alone form, has specifically been shown to be efficacious in reducing stress and anxiety [44]. Moreover, two pilot and open-label studies have led to positive results with depression [48, 49]. However, little is known about the effects of RFB when used in combination with improvisational music therapy. Our own exploratory studies indicate that clients of the RFB conditions might be able to open up more and express more therapeutically relevant emotions during the sessions, both on the verbal and musical levels, which, in turn, should lead to better therapy outcomes.

Regarding the implementation of RFB, we will not be using any biofeedback apparatus as would be done with HRVB. Instead, we will be determining each participant’s resonance frequency beforehand, using the protocol described by Lehrer [50]. This alternative approach to HRVB is possible because the resonance frequency has been shown to be stable in adults [41]. Once their resonance frequency has been established, a tablet with a breathing app set at the correct speed will be used for cueing the participants during RFB. Furthermore, we will be using an inhalation/exhalation ratio of 40/60, because longer exhalations are known to support parasympathetic activation [51]. RFB will be performed for 10 min at the beginning of each session, with the participants sitting in an upright position and the tablet placed in front of them.

#### Treatment fidelity and training the clinicians

The intervention will be conducted through 11 clinically trained music therapists (according to Finnish music therapy training standards) who have a long experience in music therapy work. Most have also participated in our previous RCT [2] and have extensive prior experience of using the IIMT model in their practice. Additionally, four of the recruited music therapists are also qualified psychotherapists.

All of the clinicians will go through intensive training to deepen their knowledge of the working principles of IIMT as well as the differing requirements of the four treatment conditions. In order to control for the role of the therapist in the groups’ outcomes, each clinician will be conducting therapy in all of the four conditions of the study.

The training period consists of 24 h of training in the IIMT model (eight weekly training sessions, 3 h each). In the training, the clinicians are presented with the idea, design, and content of the No Pain No Gain (NPNG) project, and are familiarised with the research measures and data collection principles they need to master for the RCT. The clinicians are, for instance, responsible for administering the continuous assessment of the perceived depression level, collecting session feedback, and implementing the audio-recording protocol for the home listening task.

First and foremost, it is crucial that the clinicians develop a common understanding of the theoretical and practical aspects of IIMT. To this end, the training includes lectures on IIMT theory accompanied by slide shows, articles, handouts, and video demonstrations that will remain available to the clinicians throughout the project. The improvisational techniques of IIMT will be demonstrated in every meeting, as well as the ways of creating a therapist–client relationship through the combination of clinical improvisation and talking. To increase the authenticity of the training, outside volunteers will be playing the client’s role.

For the clinical work phase, a compendium has been created from which the clinicians are advised to check the essential elements and contents of the model when needed. In addition, the members of the NPNG research group are available during the trial for any urgent needs, questions, or problems that might arise on a daily basis.

Throughout the NPNG project, the clinicians meet together every 2 weeks for group supervision. In these meetings the clinicians are supposed to focus on their own sessions and raise the most challenging issues encountered in their clinical work, with the aim of discussing and solving them. The supervision meetings are peer based, meaning there is no specific or external supervisor in charge of them. Instead, the therapists are all contributing according to their own expertise, four of them being trained supervisors through their psychotherapy qualification. Video and audio material from the sessions will be available for supervision purposes. In addition to peer-based supervision work, external supervisors/experts will be invited whenever the situation requires. The supervision sessions are also an opportunity to remind the therapists about the principles of the treatment model.

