**Methods/design:**

A 2 × 2 factorial randomised controlled trial will be carried out at a single centre in Finland involving 68 adults with a diagnosis of depression (F32 or F33 in International Statistical Classification of Diseases and Related Health Problems 10th revision). All participants will receive 6 weeks of bi-weekly IIMT, where they are invited to improvise music and reflect on those improvisations with a music therapist in a one-to-one setting. Potential enhancements to IIMT will include: home-based listening to recorded improvisations (LH) from IIMT sessions to facilitate integration of therapeutic processing into daily life; and resonance frequency breathing (RFB), a breathing exercise at the beginning of each session to facilitate emotional expression and processing. Participants will be randomised in a 1:1:1:1 ratio into each combination (IIMT alone or with one or both enhancements). The primary outcome is depressive symptoms measured by the Montgomery–Åsberg Depression Rating Scale (MADRS) at 6 weeks. Secondary outcomes are depressive symptoms at 6 months; anxiety, quality of life, and functioning at 6 weeks and 6 months; and adverse events. Secondary underlying mechanisms/process variables are self-rated momentary depression level before every IIMT session; and homework compliance in IIMT + LH. Statistical analyses involve an intention-to-treat approach, using a linear mixed-effects model examining the main effects (LH vs no LH; RFB vs no RFB) and interaction effects (LH × RFB).

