#### Randomisation and sample size

Figure 1 shows how participants eligible for the randomised controlled trial (RCT) flow through the study from recruitment to follow-up. After screening and diagnosis, 68 participants will continue to take part in the study. Following a baseline assessment they will be randomly assigned to one of the four combinations of conditions (*n* = 34 in each condition; *n* = 17 in each combination).

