**Fig. 1 Fig1:**
[figure not shown]
RCT flow chart with outcome measures. GAF Global Assessment of Functioning, HADS-A Hospital Anxiety and Depression Scale—anxiety subscale, IIMT integrative improvisational music therapy, LH listening homework, MADRS Montgomery-Åsberg Depression Scale, RAND-36 quality-of-life survey, RFB resonance frequency breathing

An external expert who has no direct contact with the patients will conduct a computerised randomisation procedure. We will employ block randomisation with randomly varying block sizes of 4 and 8. The allocation list will be saved on a password-protected repository with access only by the PI and study coordinator. To ensure allocation concealment, the randomisation will be conducted at another site (Uni Research, Bergen, Norway). As a result, the assessor, the therapists, and the participants will not be able to know the group allocation in advance. Only the outcome assessor will remain blinded to the group allocation throughout the trial. At the time of assessments, participants will be reminded not to reveal their allocation to the assessor. As far as the PI is concerned, he is blinded from the randomisation and the clients’ conditions in general, but because he is also one of the clinicians and participates in supervision he will get to know the condition of some clients. However, the PI is not involved in the client assessments or data entry in any way.

A power calculation was carried out for the primary outcome (depressive symptoms measured by the MADRS), based on the following assumptions.

Prior reviews of music therapy used in the treatment of depression have reported large effect sizes of music therapy compared to standard care. A recent meta-analysis [1], which included nine studies and involves a total of 421 participants, examined the short-term effect of music therapy for depression for primary outcomes. These authors found moderate quality evidence favouring music therapy and treatment as usual (TAU) over TAU alone for both clinician-rated depressive symptoms (SMD – 0.98, 95% CI – 1.69 to − 0.27, three RCTs, one CCT, *n* = 219) and patient-reported depressive symptoms (SMD – 0.85, 95% CI – 1.37 to − 0.34, three RCTs, one CCT, *n* = 142). Regarding IIMT specifically, our previous study found a medium effect size of *d* = 0.65 [2] based on the traditional two-arm design (intervention vs control).

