### Statistical analyses and data management

The statistical analyses will follow an intention-to-treat approach, using all available data regardless of whether the treatment was received as intended. Furthermore, in the event of missing outcome data, participants will remain in the analysis if at least one follow-up time point is available. Sensitivity analysis will be conducted with multiple imputation for missing data and as a per-protocol analysis (treatment as received). All outcome measures (MADRS, HADS, RAND-36, GAF, one-item rating of current depression severity) provide continuous data and will be examined for normality before statistical tests are conducted. The main effects of each intervention (LH vs no LH; RFB vs no RFB) and their interaction (LH × RFB) will be tested for all outcome measures, using a repeated-measures linear mixed-effects model with LH and RFB as factors. This analysis strategy has the advantage of making full use of the factorial design, such that all 68 participants are available for each comparison (as presented in Table 1). All tests will use two-sided 5% significance level, with no adjustments for multiplicity; secondary outcomes will therefore be regarded as exploratory. No interim analyses of effects will be conducted.

Most of the data obtained through scales, questionnaires, and forms will be collected electronically. Should the data be obtained through paper forms, they will be immediately converted to electronic data. Data entries are always made by an assessor who is very familiar with the assessment instruments and can thus easily recognise inaccurate data. The assessor will also double-check the data entries. All of the collected data will be stored on secure servers from the University of Jyväskylä, which includes daily backups. Dedicated password-protected folders will be used for different types of data, with access rights granted only to those researchers allowed to handle the given data.

Personal records of the participants, such as names, contact details, and consent forms, are stored in a locked room, with access only by the PI, assessor, and study coordinator. In all other contexts, client codes will be used instead of personal information.

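### Therapist is crossed with condition to control for it, but the stated randomisation does not secure that crossing and the stated model does not use it

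*Protocol article*

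**What the plan says.** Under Treatment fidelity and training the clinicians, the protocol article states the number of therapists: "The intervention will be conducted through 11 clinically trained music therapists". It gives a purpose, "In order to control for the role of the therapist in the groups’ outcomes", and the means: "each clinician will be conducting therapy in all of the four conditions of the study".

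Under Randomisation and sample size, the scheme is "We will employ block randomisation with randomly varying block sizes of 4 and 8". It is run by an external expert at another site, and no stratification factor is named. The Abstract gives the ratio: "Participants will be randomised in a 1:1:1:1 ratio into each combination". The target is 68 clients, 17 per combination and 34 per level of each factor. The article does not say how or when a client is matched to a therapist.

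Under Statistical analyses and data management, main effects and interaction are tested "using a repeated-measures linear mixed-effects model with LH and RFB as factors". Therapist is not mentioned there, either as a fixed or as a random effect. The power statement is for a plain two-sample t test.

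**The concern.** A design that deliberately balances a factor should normally be analysed with that factor in the model. Here the article makes an explicit claim of control, and two places on which the claim depends do not carry it through. The randomisation is balanced across the trial, not within therapist, so the crossing has to come from a step that is not described. The named model terms do not use the crossing even if it is achieved.

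At stake are the accuracy of the standard errors for LH and RFB and some precision, in a trial that reports only 50% power for LH. The claim about the therapist's role is also at stake if coverage turns out to be uneven. Therapists plausibly matter to the added components: under LH, the therapist may recommend improvisations and discusses the listening in later sessions. The effect of a component could therefore differ between therapists.

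**Working it through.** **Inputs from the article.** 68 clients, 11 therapists, four conditions at 1:1:1:1, blocks of 4 and 8, 34 against 34 per main effect, two-sided 5% level, d = 0.48 (LH) and d = 0.8 (RFB).

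**Assumptions.** The article gives neither caseloads nor an ICC. I take nearly equal caseloads (nine therapists with 6 clients, two with 7, since 9 × 6 + 2 × 7 = 68) and an ICC of 0 to 0.20. The simulations analyse a single endpoint with LH and RFB in the model, in line with the article's power statement, not the full repeated-measures model.

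**1. The stated power reproduces.** The noncentrality is d × √(34/2): 0.48 × 4.123 = 1.98 and 0.8 × 4.123 = 3.30. With 66 degrees of freedom, power is 49.6% and 90.2%, against the stated 50% and 90%.

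**2. Is full crossing feasible, and does the randomisation give it?** 68/11 = 6.2 clients per therapist and 68/44 = 1.5 per therapist-by-condition cell, so it is feasible. For m independent draws, the chance that a therapist sees all four conditions is 1 − 4(3/4)^m + 6(1/2)^m − 4(1/4)^m.

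- m = 6: 1 − 0.712 + 0.094 − 0.001 = 0.381
- m = 7: 1 − 0.534 + 0.047 − 0.000 = 0.513

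Expected number of therapists with full coverage: 9 × 0.381 + 2 × 0.513 = 4.5. Simulating the actual blocks (20,000 trials, therapist assigned without regard to arm) gives 44% of therapists, or 4.8 of 11. All 11 are covered in about 0.03% of trials or fewer.

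**3. Therapists differ only in average outcome.** In the balanced case each therapist's clients are spread over the four conditions in blocks of 4. Power is for the LH or RFB effect with therapist left out and with therapist included as a fixed effect (4,000 runs).

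| ICC | d = 0.48, omitted | d = 0.48, included | d = 0.8, omitted | d = 0.8, included |
|---|---|---|---|---|
| 0 | 49.6% | 48.7% | 89.6% | 88.3% |
| 0.05 | 49.0% | 49.6% | 90.6% | 90.6% |
| 0.10 | 49.7% | 52.2% | 90.9% | 91.7% |
| 0.20 | 50.6% | 57.6% | 91.9% | 94.4% |

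For LH, the gain from including therapist is about −1, 1, 2.5 and 7 points.

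Type I error with therapist omitted is 3.7% at ICC 0.10 and 3.7% at ICC 0.20; a repeat with 10,000 runs gave 4.3% and 3.8%. The direction follows from the algebra. Under perfect balance the therapist intercept cancels, so the true variance is (1 − ICC) times what the test estimates. At ICC 0.10 the effective critical value is 1.96/√0.9 = 2.07, or 3.9%. With 6 or 7 clients per therapist, balance is only approximate.

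Under arm-blind matching, type I error with therapist omitted is 5.1% to 5.6%.

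**4. The LH effect varies by therapist.** Let τ be the SD of the effect across therapists, in outcome SD units. With balanced crossing and ICC 0, the test estimates a variance of about (2 + τ²)/34. The true variance is about 2/34 + τ²/11.

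- τ = 0.3: 0.0615 against 0.0670, ratio 1.09, type I error about 6.0%
- τ = 0.5: 0.0662 against 0.0816, ratio 1.23, type I error about 7.7%

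Simulation over ICC 0 to 0.20 gives about 4.5% to 6.5% at τ = 0.3 and about 6.3% to 8.8% at τ = 0.5, taking random and balanced matching together. The same reasoning applies to RFB.

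**The case against.** The best defence is that crossing therapists with conditions is itself a design control. It guards against therapist confounding whether or not therapist is in the model, and the article promises no model adjustment. That stands. A reader might infer that the control is not delivered at all; the documents do not support that.

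A reader might also infer that therapists must have been chosen with knowledge of the arm. That does not follow. A prepared list pairing therapist with condition would also work, and the article is silent on the step. The figure of about 5 in 11 shows that an arranged step is needed, not that it was missing.

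A third tempting reading is that ignoring clustering inflates false positives. With therapists differing only in average level it does not: the error rate stays near 5%, or falls below it under balanced crossing. Inflation needs effects that differ between therapists, and that rests on an assumed SD.

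It can also be said that naming LH and RFB as factors is not a full model specification, since time and participant terms are not listed either, and that a fuller plan may include therapist. That is possible, and it limits the point to what the article states. But the article itself makes the claim of control and describes the model meant to answer the question, and the two should agree.

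**Conclusion.** The point holds in a limited form. The article's control for therapist depends on a crossing that its trial-wide randomisation does not secure by itself, and its stated model does not use that crossing.

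The consequences are modest. With crossing achieved and therapists differing only in level, the standard errors are somewhat too large, and LH loses about 0 to 3 power points at ICC 0.05 to 0.10 and about 7 at ICC 0.20. With effects that vary by therapist (SD 0.3 to 0.5), the test runs at about 5% to 9% instead of 5%. These sizes rest on assumed ICCs, assumed effect variation and nearly equal caseloads, none of which the article gives. Nothing here shows that the comparison of conditions is biased.

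**What to change.** 1. Add a random intercept for therapist to the primary mixed model. It is preferable to fixed therapist effects, which use 10 degrees of freedom. If matching was arm-blind, fixed effects would lower LH power from 49% to 43% at ICC 0.
2. Report the number of clients by therapist and condition. If the table shows incomplete crossing, limit the claim of therapist control accordingly.
3. Add a sensitivity analysis that lets the LH and RFB effects vary by therapist. The intercept alone does not address such variation. With about 1.5 clients per therapist-by-condition cell this analysis will be imprecise, and it should be labelled so.

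The cost is one variance term in the primary model, with little or no gain if the therapist ICC is near zero. The Trial status section says assessments continue until the end of 2019, so the change can be fixed before the analysis. Changing the randomisation or the assignment of therapists is not proposed. The same section reports the therapy processes completed by the end of March 2019, and fixed blocks of 4 within an unblinded therapist would have weakened concealment.
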